## 7. ASSESSMENTS & FOLLOW-UP

### 7.1 Routine Follow-up

The main part of the trial will run for 5 years, with recruitment being completed within the first 12-18 months. All patients will continue follow-up visits to a common closing date. After this final visit, data on a few key parameters will continue to be collected by annual retrospective review of the patients' routine clinic visit records for a period of up to 5 years.

The assessments are listed in the trial schedule (see section 1.3). Trial visits and assessments will correspond closely to routine clinical care, with 12-weekly visits throughout the trial. Patients randomised to the PI monotherapy arm will have additional visits at Week 4 and Week 8. Additional visits for VL testing will be required at 4-12 weeks following any VL result  $\geq 50$  copies/ml (see section 7.1.6). Data will be entered on the CRF at each visit.

#### 7.1.1 Week 4

This visit is only required for patients randomised to the ***PI monotherapy arm***.

The visit window is  $\pm 2$  weeks from the target visit date. The visit will be scheduled to occur in the morning due to the requirement for fasting blood tests. Patients should be instructed to not eat or drink anything (except plain water) from midnight before the visit. They should be instructed not to take any morning dose of PI medication (other medication can be taken) until after the blood has been drawn. The following assessments will be performed:

- Review of symptoms
- Review of concomitant medications
- Adherence to ART (no. of missed doses in previous 2 weeks and since last visit)
- Targeted physical examination (as needed to evaluate reported symptoms)
- Review of healthcare resource utilisation since last visit (patient self-report and review of case sheet)
- EQ-5D health status questionnaire
- Laboratory tests:
  - HIV viral load
  - Full blood count (haemoglobin, white cells, neutrophils, lymphocytes and platelets)
  - Biochemistry (sodium, potassium, urea, creatinine, bilirubin, ALT, alkaline phosphatase)
  - Fasting glucose
  - Fasting lipids (total cholesterol, triglycerides, LDL, HDL)
  - PI drug concentration (trough level preferred, or at least 4 hours from last dose)
  - Plasma storage (1 X 4ml EDTA sample)

#### 7.1.2 Week 8

This visit is only required for patients randomised to the ***PI monotherapy arm***.

The visit window is  $\pm 2$  weeks from the target visit date. The patient should be instructed not to take any morning dose of PI medication (other medication can be taken) until after they have been assessed in the clinic, in case a repeat PI drug level concentration may be required. If the trough level result at Week 4 is known to be above the threshold, then the patient can be instructed prior to the visit that the morning PI dose can be taken as scheduled (because a repeat drug concentration level will not be needed at Week 8). Adjustment to PI dose, ritonavir dose or drug schedule may be made at this visit depending on the results of PI levels measured at Week 4 (these will be available at this visit).

The required assessments at this visit are:

- Review of symptoms
- Review of concomitant medications
- Adherence to ART
- Review of healthcare resource utilisation since last visit (patient self-report and review of case sheet)
- EQ-5D health status questionnaire
- HIV viral load

Optional:

- PI drug concentration (trough level preferred, or at least 4 hours from last dose). This is only indicated if the Week 4 drug concentration was below the threshold and the clinician thinks it appropriate to recheck the level.

### 7.1.3 Week 12

This visit is required for ***all patients.***

The visit window is -2 to + 6 weeks from the target visit date. The visit will be scheduled to occur in the morning due to the requirement for fasting blood tests. Patients should be instructed to not eat or drink anything (except plain water) from midnight before the visit.

Patients on PI monotherapy arm who had a low PI concentration at Week 4 and for whom the clinician has decided that a further check on drug levels is warranted (for example if a dose adjustment has been performed at week 8) should be instructed not to take any morning dose of PI medication (other meds can be taken) until after the blood has been drawn. All other patients can take their morning medication as scheduled. The following assessments will be performed:

- Review of symptoms
- Review of concomitant medications
- Adherence to ART (no. of missed doses in previous 2 weeks and since last visit)
- Targeted physical examination (as needed to evaluate reported symptoms)
- Neurocognitive assessment
- Review of healthcare resource utilisation since last visit (patient self-report and review of case sheet)
- EQ-5D health status questionnaire (self-completed by patient)
- MOS-HIV quality of life questionnaire (self-completed by patient)
- Laboratory tests:
  - HIV viral load
  - CD4+ count
  - Full blood count (haemoglobin, white cells, neutrophils, lymphocytes and platelets)
  - Biochemistry (sodium, potassium, urea, creatinine, bilirubin, ALT, alkaline phosphatase)
  - Bone profile (calcium and phosphate)
  - Fasting glucose
  - Fasting lipids (total cholesterol, triglycerides, LDL, HDL)
  - Urine protein / creatinine ratio
  - Plasma storage (1 X 4ml EDTA sample)

Optional:

- PI drug concentration (trough level preferred, or at least 4 hours from last dose). This is only indicated for patients in the PI monotherapy arm in whom the Week 4

drug concentration was below the threshold and for whom the clinician thinks it appropriate to recheck the level.

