| Symptom review/ physical examination                     | X                           | X                   | X                       | X                 | X                    | X                                                         | X                                                                                    |
| Assessment of clinical adverse events                    |                             | X                   | X                       | X                 | X                    | X                                                         | X                                                                                    |
| Cardiovascular risk assessment                           | X                           |                     |                         |                   |                      |                                                           | X                                                                                    |
| ECG (within last 6 months acceptable)                    | X                           |                     |                         |                   |                      |                                                           |                                                                                      |
| Assessment of healthcare resource utilisation            |                             |                     | X                       | X                 | X                    | X                                                         | X                                                                                    |
| EQ-5D health status questionnaire                        |                             | X                   | X                       | X                 | X                    | X                                                         | X                                                                                    |
| Neurocognitive assessment                                |                             | X                   |                         |                   | X                    |                                                           | X                                                                                    |

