| MOS-HIV questionnaire                                    |                             | X                   |                         |                   | X                    |                                                           | X                                                                                    |
| HIV viral load                             | X                           | X                   | X                       | X                 | X                    | X                                                         | X                                                                                    |
| CD4+ count                                               | X                           | X                   |                         |                   | X                    | X                                                         | X                                                                                    |
| Full blood count, UEC and LFTs               | X                           | X                   | X                       |                   | X                    | X                                                         | X                                                                                    |
| Bone profile                                 | X                           |                     |                         |                   | X                    | X                                             | X                                                                                    |
| Glucose and lipids (fasting)                 | X                           |                     | X                       |                   | X                    |                                                           | X                                                                                    |
| Hepatitis B/C serology (within last 6 months acceptable) | X                           |                     |                         |                   |                      |                                                           | X                                                                                    |

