- 3 FBC will include Hb, WCC, neutrophil count, lymphocyte count, platelets; UEC will include sodium, potassium, urea, creatinine; LFTs will include bilirubin, ALT, alkaline phosphatase.
- 4 Bone profile (calcium and phosphate) and urine protein/creatinine ratio will be performed at screening, Week 12 and annual visits in all, but quarterly only in those patients taking tenofovir.
- 5 Lipids will include total cholesterol, triglycerides, LDL, HDL. If elevated at Week 12, additional fasting lipid tests can be performed between the annual visit checks as needed to inform clinical management.
- 6 Blood sample will be stored at screening (2X4ml EDTA), Baseline, Week 12 and annual visits (1X4ml EDTA) plus any visit where a second VL sample is taken for confirmation of rebound (2X4ml EDTA).
- 7 PI drug concentration measurement can be repeated at Week 8 and/or Week 12 if Week 4 concentration is low (only in the PI monotherapy arm).
- 8 Pregnancy test in women only; can be urine or blood test, as per standard practice at site; repeated at any subsequent visits where pregnancy is suspected.
- 9 The final visit will be scheduled within 12 weeks before the common closing date of the trial.

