### **5.3 Post-randomisation procedures and follow-up**

The clinician will complete a prescription with the patient's details and trial medication as allocated. The prescription will be for 3 months, or until the next protocol-mandated trial visit (see section 6.4).

Trial visit schedules will be sent by email or fax to the site at the time of randomisation. Patients should be followed on the same schedule even if their trial medication is discontinued. The target dates for trial visits are determined by the date of randomisation and are not affected by subsequent events. The schedule defines visit dates (with windows) necessary for data collection, but the patient may be seen more frequently for clinical care as needed.

Patients in the PI monotherapy arm will be asked to return in 4 weeks (visit window  $\pm 2$  weeks). The Week 4 visit should be scheduled for the morning, and patients should be instructed not eat or drink anything (except plain water) from midnight before the visit. They should also be instructed to omit any morning dose of PI medication, and bring the medication with them to the clinic. They may take any other necessary dose of routine medication as usual.

Patients randomised to continue triple-therapy will be asked to return in 12 weeks. The Week 12 visit should be scheduled for the morning, and they should be instructed not to eat or drink anything (except plain water) from midnight before the visit. They may take all their medication as usual.

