#### 9.2.2 Secondary outcome measures

- **Serious drug or disease-related complication**

Defined as the first occurrence of one of the following in any individual patient:

- **Death from any cause**
- **Serious AIDS-defining illness** (see diagnostic criteria, Appendix 7)
- **Serious non-AIDS defining illness** (see diagnostic criteria, Appendix 8)
  - Acute myocardial infarction
  - Coronary artery disease requiring invasive procedures
  - Cirrhosis
  - Acute liver failure
  - End-stage renal disease
  - Stroke
  - Clinical acute pancreatitis
  - Severe lactic acidemia
  - Severe facial lipoatrophy
  - Severe peripheral neuropathy
  - Non-AIDS malignancy

- **Adverse events**

Defined as the total number of Grade III and IV adverse events.

- **Confirmed Virological rebound**

Defined as 3 consecutive VL tests  $\geq 50$  copies/ml, with at least 4 weeks between the first and last test. One of these 3 tests may be a repeat of the same sample. There are a number of alternative definitions for virological rebound, each of which has advantages and limitations (28). The alternative definitions to be used in this trial will be described in the full statistical analysis plan.

- **CD4+ count change**  
Defined as change from baseline in absolute CD4+ count.
- **Health-related Quality of Life change**  
Defined as change from baseline in the mental and physical health summary scores.
- **Neurocognitive function change**  
Defined as change from baseline in the neurocognitive function summary score.
- **Cardiovascular risk change**  
Defined as change from baseline in the risk of cardiovascular disease calculated from the Framingham equation (19).
- **Health care costs**  
Defined as the total cost of health care resources utilised per patient year.

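### Safety laboratory tests are scheduled unequally between the arms (week 4 bloods in the PI arm only, quarterly bone and urine tests in tenofovir users only), and the Grade III/IV comparison makes no allowance for it

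*Combined protocol and SAP*

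**What the plan says.** **Visits.** Section 7.1 of the protocol says that "Patients randomised to the PI monotherapy arm will have additional visits at Week 4 and Week 8". For control, section 5.3 says "Patients randomised to continue triple-therapy will be asked to return in 12 weeks".

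**Tests at the extra visits.** In the trial schedule (1.3), the row "Full blood count, UEC and LFTs" is marked at week 4 in a column headed for the PI arm only. It is not marked at week 8, and from week 12 it applies to both arms. Fasting glucose and lipids are marked at week 4 (PI arm), week 12 and annually. The row "Assessment of clinical adverse events" is marked at both week 4 and week 8. Section 7.1.2 requires only a viral load in the week 8 laboratory work, with an optional drug level.

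**Tests tied to a drug.** Footnote 4 of the schedule and section 7.1.4 give bone profile and urine protein/creatinine to everyone at screening, week 12 and annual visits, but "quarterly only in those patients taking tenofovir".

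**Outcome and analysis.** Section 7.3 grades clinical and laboratory adverse events on one scale. Section 9.2.2 sets the outcome: "Defined as the total number of Grade III and IV adverse events". Section 9.5.2 tabulates these events by body system and arm and compares the arms by chi-squared test. Neither section limits the count to visits or tests common to both arms. Neither says whether one abnormality seen at weeks 4 and 12 counts once or twice.

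**The concern.** Safety and toxicity is the second trial objective (2.4.1), and reduced long-term toxicity is one of the benefits put forward for monotherapy (2.5.5). A count of events depends on how often one looks. Several Grade 3 laboratory values in Appendix 6 need no symptoms: ALT 5.1 to 10.0 times the upper limit of normal, bilirubin 2.6 to 5.0 times, triglycerides 8.49 to 13.56 mmol/L. Such a value at week 4 that has resolved by week 12 becomes an event in the PI arm. In a control patient no scheduled test would reveal it. The reverse can happen later for calcium and phosphate, which are checked quarterly only in tenofovir users. A difference between the arms in laboratory toxicity could then reflect the testing calendar rather than the treatments.

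**Working it through.** **1. The plan's own figure.** Section 12.1.2 states 2 extra monitoring blood tests in the PI arm in the first 6 months. Week 4 plus week 8 gives 1 + 1 = 2, which agrees. Only the week 4 test carries safety laboratory work.

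**2. Scheduled post-baseline assessments, PI v control.** Visits at weeks 12, 24, …, 192 number 192/12 = 16. Glucose and lipids fall at weeks 12, 48, 96, 144 and 192, so 5 times.

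| Assessment | To week 12 | To week 192 |
|---|---|---|
| Clinical adverse events | 3 v 1 | 18 v 16 (2/16 = 12.5% more) |
| Blood count, renal, liver | 2 v 1 | 17 v 16 (1/16 = 6% more) |
| Fasting glucose and lipids | 2 v 1 | 6 v 5 (1/5 = 20% more) |
| Bone and urine, not on tenofovir | 1 v 1 | 5 v 5 |
| Bone and urine, on tenofovir throughout | 1 v 1 | 16 v 16 |

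A separate final visit adds one to each arm. For follow-up of 156 to 260 weeks, blood panels run from 14 v 13 (8% more) to 22 v 21 (5% more).

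**3. Early detection.** Assume equal true incidence, onset uniform over weeks 0 to 12, and duration D weeks. Control is tested at week 12, so detection is D/12. The PI arm is also tested at week 4, which adds onsets between max(0, 4 − D) and 4 that the week 12 test does not already catch.

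| D (weeks) | PI | Control |
|---|---|---|
| 2 | 4/12 = 33% | 2/12 = 17% |
| 4 | 8/12 = 67% | 4/12 = 33% |
| 6 | 10/12 = 83% | 6/12 = 50% |
| 8 | 12/12 = 100% | 8/12 = 67% |
| 12 | 100% | 100% |

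The gap exists only for abnormalities lasting less than 12 weeks.

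**4. The opposite asymmetry.** Control patients keep their NRTIs (6.2.1) and PI-arm patients stop them (6.3.1). Tenofovir belongs to that class, so its users should be mainly in control, apart from PI-arm patients who return to triple therapy. Let s and t be the shares on tenofovir throughout in control and PI. Mean bone and urine tests per patient to week 192 are 5 + 11s and 5 + 11t, a control excess of 11(s − t). The documents give neither share. With t = 0 the excess runs from 0 (s = 0) through 5.5 (s = 50%) to 11 (s = 100%), against one extra PI-arm blood panel. Test counts do not convert into event counts, because the analytes differ. Appendix 6 grades calcium and phosphate to Grades 3 and 4, but grades proteinuria from a random or 24-hour collection and not from the ratio, so the bone profile is the more direct route.

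**5. Effect on the test, illustrated.** Take 560/2 = 280 patients per arm, no true difference, and the chi-squared test applied to patients with at least one event. Suppose the extra looks add a detection in a share q of patients otherwise event-free, so p₁ = p₀ + (1 − p₀)q. With p₀ = 10% and q = 2%, p₁ = 0.10 + 0.90 × 0.02 = 0.118. False-positive rate, nominal 5%:

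| q | p₀ = 10% | p₀ = 30% | p₀ = 50% |
|---|---|---|---|
| 1% | 6.4% | 5.4% | 5.2% |
| 2% | 10.5% | 6.5% | 5.6% |
| 5% | 36.8% | 14.4% | 9.1% |

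The documents give neither p₀ nor q. This is a range and not an estimate, and it ignores the tenofovir tests in step 4.

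**The case against.** **Clinical events.** A reader might infer from the 3 v 1 assessments before week 12 that severe clinical events are also over-counted. The documents do not support much of that. Grade 3 clinical events in Appendix 6 generally mean inability to carry out usual activities, so most should be recalled at week 12. Section 11.2.1(d) requires an Event CRF for any Grade 3 or 4 event in either arm. Sections 5.3 and 7.3 also allow extra visits and safety tests when clinically needed. This part of the objection stands, but the Event CRF cannot report a laboratory value that nobody measured.

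**Whole-trial direction.** A reader might infer that the total Grade III/IV count is biased against monotherapy. The tenofovir-only tests probably run the other way, so that is not shown.

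**Footnote 5.** The schedule says "If elevated at Week 12, additional fasting lipid tests can be performed between the annual visit checks". This might be read as extra testing of the PI arm, but it applies to any patient in either arm and is not an arm difference as written.

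**Extent of week 4.** It is not a full safety panel, since bone profile and urine protein/creatinine are omitted.

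**Real toxicity.** Section 2.5.1 accepts that some PI-arm patients start a new PI and may have new side effects. Part of any early excess would be genuine, and removing week 4 findings from the main comparison could hide it. That stands and shapes the fix.

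**Status of 9.5.2.** Section 9.5 promises a full analysis plan, which is not among these documents. It is to be based on this summary, so the gap carries forward unless it is filled there.

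**Conclusion.** The concern holds in a limited form. As planned, transient and symptomless Grade III/IV laboratory events in the first 12 weeks are over-detected in the PI arm. This follows from the schedule whenever true incidence is equal and duration is under 12 weeks; the size (for example 67% v 33% at four weeks) rests on uniform onset. A second asymmetry, in bone and urine tests, probably favours detection in control after week 12, which assumes that tenofovir use is concentrated there. The net direction for the total count is therefore not established. The effect on the total is probably modest: one extra panel in 17 v 16, and 6 v 5 for glucose and lipids, over 192 weeks. The false-positive figures rest on assumed inputs and show only that small added detection matters more when events are uncommon. Clinical events are little affected and the primary endpoint is untouched. The early monitoring itself is a stated safety measure and is not at fault. The gap lies in comparing its findings without allowance.

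**What to change.** Change section 9.5.2 and carry the change into the full analysis plan:

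- Keep the full Grade III/IV count, with clinical events at any date, as the main safety table.
- Add a pre-specified between-arm comparison of Grade III/IV laboratory events, restricted to tests scheduled for all patients in both arms at the same visits. That means week 12 onward, with bone and urine tests from week 12 and annual visits only, and unscheduled repeats excluded.
- Base any statement about a difference in laboratory toxicity on both tables.
- Report the PI-arm week 4 laboratory findings separately.

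After this, scheduled laboratory tests to week 12 are 1 v 1 in the restricted comparison, and bone and urine tests to week 192 are 5 v 5 whatever the drug. The cost is one extra table and a short addition to the text, with no change to any visit or sample. The restricted comparison omits some real early PI-arm laboratory events; these remain in the main count.
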